### Sample description

Women of reproductive age will be selected from those referred to the hospital for contraception from primary care units in the Northern Zone of the city of São Paulo or the Gynecological Emergency Department of the Mandaqui Hospital Complex.

### Inclusion and exclusion criteria

The study will include women aged 18–50, with no restrictions on race or socioeconomic status. Both nulliparous and multiparous women will be considered eligible, provided they meet other criteria established to ensure the safety and appropriateness of the IUD placement procedure.

Conversely, women with suspected or confirmed pregnancy, a history of diagnosed chronic pain, or active pelvic infection will be excluded from the study. Women who took pain medication within 12 hours before the procedure will be excluded to prevent interference with pain perception. Women with known contraindications for IUD placement, such as significant uterine cavity distortion, active pelvic inflammatory disease, or Wilson’s disease, will be deemed ineligible [4]. Other exclusion criteria include copper allergy, unexplained abnormal uterine bleeding [4], a history of photosensitivity, or any condition affecting the lumbar region, such as active neoplasms, established osteomyelitis, or pre-existing deep tissue injuries with necrosis or infection. The participants will not be permitted to participate in any other clinical study during the trial.

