## Introduction

Unplanned pregnancy affects up to 65% of women in some areas of Brazil, increasing the risk of unsafe abortions and inadequate prenatal care, which significantly contribute to maternal mortality. Ensuring access to long-acting contraceptive methods, such as the copper intrauterine device (IUD), is crucial in reproductive planning [1,2]. Despite its effectiveness, only 4.4% of women use an IUD, with many opting for birth control pills or sterilization [3]. The IUD is suitable for most women of reproductive age, including adolescents, and is also indicated for emergency contraception and controlling heavy uterine bleeding [4].

Despite these benefits, pain during placement causes fear and reluctance among patients and constitutes a significant barrier to IUD adoption [5,6]. While broader social and cultural determinants influence IUD uptake, insertion-related pain is an immediate, modifiable procedural factor that may directly affect both pain perception and anticipatory fear. Visceral pain arises from cervical dilation, with afferent nerves transmitting impulses via the T10-L1 dermatomes [7], while somatic pain results from pelvic floor distension, involving the S2-S4 dermatomes [8]. Evidence of adequate pain control remains inconclusive, as studies involving the use of non-steroidal anti-inflammatory drugs (NSAIDs), local anesthetics, and cervical preparation methods have demonstrated limited effectiveness [2,5–7]. A Cochrane review found that 2% lidocaine gel, misoprostol, and most NSAIDs failed to reduce pain during IUD placement, with only some formulations of lidocaine, tramadol, and naproxen having effects in specific groups [6].

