### Sample size calculation

The total sample size will be 72 participants. This number was calculated to provide an 80% power (α = 0.05) with an effect size of 0.14. The number of patients per group was determined using a sample size calculation with G*Power 3.1.9.7. The sample was calculated for two groups, and 8 measurements will be performed: at baseline, during the IUD insertion phases (Pozzi, hysterometry, and IUD placement), at 5 and 15 minutes after placement, and at 24 and 48 hours after the procedure.

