### Collection of patient history and risk factors

The patient history will be collected from all participants using a questionnaire. In addition to general demographic data (age, sex, marital status, occupation, educational level, and income), the medical history will cover chief complaints, current disease status, past medical history, medications in use, smoking, alcohol consumption, the use of systemic antibiotic therapy in the previous 12 months, hospitalization or infection (including skin infections) in the previous 12 months, previous IUD use, and preferred contraceptive methods. This questionnaire will enable the correlation of clinical, demographic, and epidemiological risk factors with the study outcomes in this population.

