### Allocation (Sequence generation, allocation concealment mechanism, implementation)

A random sequence generator available online (https://www.sealedenvelope.com/) will be used to select the block randomization option with two treatments at a 1:1 ratio, resulting in equal numbers of patients in each group (n = 36 per group). As the total sample size is 72 patients, 12 blocks of six patients each will be established. Opaque envelopes will be sequentially numbered (1–72) and will contain the randomized group allocation. These envelopes will be sealed and stored securely until the IUD is placed. Only the designated researcher responsible for treatment will be aware of the assigned intervention. After opening, the envelope will be resealed and stored with the patient’s medical record, remaining concealed until the final statistical analysis. An individual not directly involved in the study will generate the random sequence and prepare the envelopes.

All participants will undergo the same IUD placement protocol performed by the same healthcare provider, as described in the “IUD Placement Protocol” section. Immediately after placement, the researcher in charge of applying PBM will retrieve and open an envelope, maintain the order of the remaining envelopes, and administer the assigned treatment (active or sham PBM). Only this researcher will be aware of the allocation.

The main investigator will oversee data storage (digital platforms) and organization. The statistician will be responsible for data analysis and will remain blinded to the interventions. The envelopes will also store participant records (patient history questionnaire, demographic data, risk factors, and statement of informed consent) and will be securely archived.

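### Women of mixed parity are eligible, but the protocol neither stratifies by parity nor names it as a baseline item, and its VAS tests cannot adjust for it

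*Protocol article*

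**What the plan says.** Four parts of the protocol article bear on this.

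- **Inclusion and exclusion criteria.** Parity is mentioned expressly: "Both nulliparous and multiparous women will be considered eligible, provided they meet other criteria". There is no quota or cap.
- **Allocation.** An online generator "will be used to select the block randomization option with two treatments at a 1:1 ratio", and "As the total sample size is 72 patients, 12 blocks of six patients each will be established". There is one envelope series, numbered 1 to 72, and no stratification factor is named.
- **Collection of patient history and risk factors.** The form is itemised in some detail. Its items related to contraception are "previous IUD use, and preferred contraceptive methods. This questionnaire will enable the correlation of clinical, demographic, and epidemiological risk factors with the study outcomes". Parity and prior vaginal birth are not named, though past medical history is listed as a broad item.
- **Statistical analysis.** Between-arm comparisons of non-normal continuous variables use the Mann-Whitney test, and VAS over time uses the Friedman test. The section adds that within-subject correlation will be accounted for, but names no model and no covariate.

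On mechanism, the Introduction says: "Visceral pain arises from cervical dilation, with afferent nerves transmitting impulses via the T10-L1 dermatomes". It does not mention parity.

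**The concern.** Three of the eight VAS readings are taken during cervical clamping, hysterometry and device placement. If pain at these steps depends on the cervix, a woman's birth history is a plausible predictor of the primary outcome, and it is the obstetric characteristic that the eligibility text singles out. As described, neither the allocation nor the named tests make use of it.

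Two things are at stake. In the one trial that is run, a chance difference in parity between arms would push the VAS difference up or down, and the named tests could not correct for it. Whether or not imbalance occurs, the spread in pain due to parity would be counted as noise, which costs power in a small trial.

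**Working it through.** **Inputs from the article.** N = 72, 36 per arm, blocks of six. The block count is consistent: 12 × 6 = 72. The sample size itself does not involve parity, so it has no bearing on this point.

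**Inputs assumed, because the article gives none.** Nulliparous share p = 0.30 to 0.50; VAS difference between parity groups δ = 1 to 2 points; VAS SD = 2.5.

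**1. Chance imbalance under the current list.** Each complete block puts three women in each arm. If women arrive independently with share p, the nulliparous counts in the arms are two independent Binomial(36, p) variables. A gap of at least 15 points means at least 6 women (5/36 = 13.9%, 6/36 = 16.7%). A gap of at least 20 points means at least 8 women (7/36 = 19.4%, 8/36 = 22.2%).

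| p | P(gap ≥ 15 points) | P(gap ≥ 20 points) |
|---|---|---|
| 0.30 | 0.156 | 0.053 |
| 0.40 | 0.185 | 0.070 |
| 0.50 | 0.194 | 0.076 |

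As a cross-check, fix the total number of nulliparous women at 22, 29 or 36 and split the 72 at random into 36 and 36 (hypergeometric). P(gap ≥ 15 points) is then 0.20, 0.15 and 0.24. The dip at 29 arises because an odd total allows only odd gaps, so the threshold becomes 7 women.

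**2. Imbalance under stratified blocks of six.** Only the last, incomplete block of a stratum can be uneven, by at most 3 women: 3/36 ≈ 8 points.

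**3. Effect of an imbalance on the result.** Shift in the arm difference = δ × gap/36. For a 6-woman gap: 1 × 6/36 = 0.17 to 2 × 6/36 = 0.33 VAS points. The standard error of the arm difference is 2.5 × √(2/36) = 0.59, so the shift is 0.28 to 0.57 of one standard error.

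**4. Variance left in the error term.** R² = p(1 − p)δ²/SD².

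- Lowest: 0.30 × 0.70 × 1/6.25 = 0.034.
- Highest: 0.50 × 0.50 × 4/6.25 = 0.16.

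**5. What adjustment recovers.** Take an effect for which the unadjusted two-sided 5% comparison has 80% power. Adjusted power = Φ((1.960 + 0.842)/√(1 − R²) − 1.960).

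- R² = 0.034: 81%.
- R² = 0.16: 86%.

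For a wider range of parity effects, with 33–50% nulliparous, adjusted power is about 81% at 0.3 SD and 89–90% at 1.0 SD.

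**The case against.** The strongest reply is that unstratified permuted blocks are a valid design for a single-centre trial of this size. Chance imbalance is already covered by the test's error rate, so there is no bias and no type I error inflation. This stands in full.

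A reader might go further than the text allows and infer that the trial can neither balance nor adjust for parity, or that imbalance could never be detected. The article does not support that. Randomisation balances parity in expectation. Past medical history may well hold obstetric history. An article condenses its form, and the full protocol and any analysis plan, which are not shown, may name parity as an item or covariate. The eligibility sentence is also permissive: it allows a mix and does not set out to create one.

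It is fair, too, that the link from parity to pain is an inference from the mechanism in the Introduction. The article never states it, and every figure for size rests on assumed values. If the parity effect is only 0.3 SD, adjustment gains about one power point.

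What remains is what the article does fix: one list without strata, an itemised form that does not name the factor, and named VAS tests that cannot use it.

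**Conclusion.** The point holds as a worthwhile improvement to the design, not as an error that invalidates it. The plan gives no protection against chance imbalance in parity beyond randomisation itself, and the tests it names forgo any precision that parity offers.

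On the assumed shares, roughly one trial in six to one in five would show a gap of 15 points or more, against a ceiling of about 8 points with stratified blocks. Such a gap would typically move the VAS difference by a fraction of one standard error. The likelier benefit is precision: a gain of about 1 to 6 power points under the assumed 1–2 point parity effect, and less if that effect is smaller. The benefit is modest, but the article lists the trial as not yet recruiting, with a start on March 30, 2026. Stratification can be set up cleanly only before the envelopes come into use.

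**What to change.** 1. Name parity as a baseline item recorded before randomisation, defined as at least one vaginal birth, yes or no.
2. Make the between-arm VAS comparison account for it, in place of the unadjusted tests. Either use a model with a parity term (a mixed model or ANCOVA) or a rank test stratified by parity. A covariate cannot simply be added to a Mann-Whitney or Friedman test, so this changes the method. A mixed model would also meet the section's own commitment to handle within-subject correlation.
3. Preferably, generate two blocked lists by parity with the same online generator, each with its own numbered envelopes. If one list is kept, steps 1 and 2 still recover the precision and allow any imbalance to be reported and adjusted for.

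**Cost.** One question, a rewritten analysis paragraph, and spare envelopes in each stratum because stratum sizes are not known in advance. The arms may no longer be exactly 36 v 36. With blocks of six the worst case is 33 v 39, when both last blocks are 3 v 0 in the same direction. Smaller blocks reduce this.

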### Study discontinuation criteria

There are no plans to interrupt or modify the allocated interventions for any participant in the trial, as the control group will receive the standard treatment recommended by the Brazilian Ministry of Health, a systematic Cochrane review [6], and the manufacturer’s guidelines for IUD placement. There is no evidence of an effective analgesic treatment for IUD placement [6]. The intervention in the experimental group is a procedure that does not cause adverse effects or complications, with previous reports indicating analgesic effects during labor [9]. As the study poses no risk to the participants, there is no criterion for study discontinuation. Given the very short duration of participant involvement in the study, no specific strategies for improving or monitoring adherence will be required.

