### Blinding (Masking)

Only the researcher in charge of administering the treatment (who opens the randomization envelopes) will be aware of the assigned intervention for each participant. The participants will be blinded because of the visual similarity of the treatments (LED on versus LED off). The researcher collecting the outcome data will also be blinded to the interventions and will not be present in the room during treatment. Group allocation will be disclosed only after the statistical analysis is completed, ensuring that the data collector and statistician remain blinded. Unblinding during the trial is not planned, as no adverse events are expected with PBM use.

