#### Secondary outcomes.

Pain description – Free narrative reportNumber of analgesics taken – Paracetamol intake recorded from baseline to 48 hours after T 380 copper IUD placement.Anxiety – Assessed using the Generalized Anxiety Disorder 7 (GAD-7) questionnaire [15] 15 minutes after IUD placement.Quality of life – Measured using the WHOQOL-Pain instrument [16] from baseline to 48 hours after placement.Patient satisfaction – Assessed through close-ended questions [6] 15 minutes after placement.Time required for relief of abdominal discomfort (menstrual cramps) – Measured in days from baseline.Verification of successful placement – Investigated dichotomously (success/failure) from baseline to 48 hours after placement.Adverse effects – Including uterine perforation, IUD displacement, abdominal pain, increased vaginal bleeding, and allergic reactions. An open-ended question will be used for the participants to report adverse effects, followed by a list of potential impacts to help them recall any unreported symptoms.Side effects – including cramps, mild pain, light bleeding, and tongue numbness. An open-ended question will be asked first, followed by a list of potential side effects to improve recall.

*Primary outcome – Pain - Visual Analog Scale (VAS)*: Pain will be assessed using the Visual Analog Scale (VAS), as illustrated below. One end of the scale is marked “0”, corresponding to the absence of pain, and the other end is marked “10”, indicating unbearable pain. The same scale will be used for all participants. The same operator will always provide instructions for marking the scale. Pain scores will be recorded, and this assessment will be performed at all study visits, including during the IUD insertion phases (Pozzi, hysterometry, and IUD placement), at 5 and 15 minutes after placement, and at 24 and 48 hours after the procedure. The participants will be asked about spontaneous pain at three distinct moments during placement: pain during clamping with the Pozzi forceps, pain during hysterometry (uterine length measurement), and pain during the actual IUD placement. All participants will receive daily phone call reminders to ensure accurate recording of their outcomes [17].

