Patient satisfaction with T 380 copper IUD placement for contraception will be assessed 15 minutes after the procedure using guiding questions [6]. The assessment will include whether the placement experience was unpleasant, whether the patient would undergo the procedure again, and whether she would recommend it to a friend.

*Secondary outcome – Time required to relieve abdominal discomfort following PBM*: The time required to relieve abdominal discomfort following PBM will be recorded in hours, measured from the onset of cramps until complete pain resolution.

*Secondary outcome – Verification for IUD placement success*: IUD placement will be assessed as a binary outcome (success/failure).

*Secondary outcome – Adverse effects (uterine perforation, IUD displacement, abdominal pain, increased vaginal bleeding, and allergy)*: An open-ended question will be asked to elicit the patient’s free responses regarding adverse effects. The responses will then be listed nominally so that the patient may recall any impact that she may have forgotten to report.

*Secondary outcome – Side effects (cramps, mild pain, mild bleeding, tongue anesthesia)*: An open-ended question will be asked to enable the patient to freely describe any side effects. Effects will then be listed by name to help the patient recall any impact that she may have forgotten to report.

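### The harm prompts include a tongue effect that fits neither procedure and none names the skin under the LED panel, while the stated absence of risk conflicts with the low risk stated elsewhere

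*Protocol article*

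**What the plan says.** The Secondary outcomes section of the protocol article lists harms twice, first in a summary and then in fuller descriptions. In the summary, adverse effects are given as "Including uterine perforation, IUD displacement, abdominal pain, increased vaginal bleeding, and allergic reactions", and side effects as "including cramps, mild pain, light bleeding, and tongue numbness". The fuller description repeats the side-effect list as "Side effects (cramps, mild pain, mild bleeding, tongue anesthesia". For both categories the woman is first asked an open question and is then taken through the named effects to aid recall.

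Table 1, under Group composition, gives the LED panel's application technique as contact.

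Study discontinuation criteria describes the trial's risk in two categorical statements. On the intervention: "The intervention in the experimental group is a procedure that does not cause adverse effects or complications". On the study as a whole: "As the study poses no risk to the participants, there is no criterion for study discontinuation". The Statistical analysis section explains the absence of interim analyses and stopping guidelines by the trial's short duration and its low risk.

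**The concern.** A prompted list exists to recover effects that a woman would not volunteer, so its items should match the procedures she undergoes. One of the four side-effect items does not: a tongue effect follows neither from placing a copper IUD nor from an LED panel held against the body. The site where the tested intervention could plausibly cause a local reaction, the skin in contact with the panel, is not named in either list.

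Harm data on PBM itself would then depend on a woman volunteering a skin reaction or regarding it as an allergy. If none were recorded, the final report could be read as confirming the prior statement that PBM causes no adverse effects, although the question was not put directly. The article's two accounts of risk add to this, since the categorical one is the one attached to the intervention.

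**Working it through.** No figure in the article bears on this point, so the check is a count and a comparison of the text.

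**1. Count of named effects (Secondary outcomes).**
- Adverse effects: uterine perforation, IUD displacement, abdominal pain, increased vaginal bleeding, allergic reactions = 5.
- Side effects: cramps, mild pain, light bleeding, tongue numbness = 4.
- Total: 5 + 4 = 9.
- Naming the skin at the irradiated site: 0 of 9.
- Able to cover a skin reaction in part: 1 of 9 (allergic reactions).
- Fitting neither IUD placement nor an LED panel: 1 of 9 (tongue).

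**2. Is the tongue item a slip in one place?** It appears in both the summary and the fuller description, with slightly different wording (numbness in one, anesthesia in the other). It is therefore part of the stated list and not a single stray word.

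**3. Is skin contact established?** Table 1 says contact. The text does not state the body site outright; the lumbar exclusions in Inclusion and exclusion criteria suggest the lower back. The point needs only that the panel touches the skin somewhere, so the fix refers to the irradiated site.

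**4. The two accounts of risk.**

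| Section | Account of risk | Decision it supports |
|---|---|---|
| Study discontinuation criteria | None; PBM causes no adverse effects | No discontinuation criterion |
| Statistical analysis | Low | No interim analyses or stopping guidelines |

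No risk and low risk cannot both be the trial's position. The two sections reach compatible decisions, so the conflict lies in the reason given and changes no conduct or analysis.

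**5. Could the trial support the categorical statement?** The active arm has 36 women (Group composition). With zero events and every event captured, the exact one-sided 95% upper bound is 1 − 0.05^(1/36) = 0.0798, or about 8.0%. This follows from the sample size alone and would be the same after the fix, so it does not measure the defect. It shows only that a clean harms table from this trial could not establish an absence of risk.

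**The case against.** The strongest reply is that capture is already adequate. The open question comes first, allergic reactions are prompted, and the summary introduces both lists as inclusive, so they may be examples; the actual form is not shown. Part of this stands: capture is partial and not absent. But the fuller description gives the lists without that qualifier, and a list that spends an item on the tongue while omitting the contact site is poorly matched to the intervention however it is read.

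A second reply is that no risk may have meant no added risk. The text does not say so.

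Several stronger readings are tempting, and the documents do not support them:

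- **That stopping PBM or sham in an individual woman is ruled out.** A reader might infer this from "There are no plans to interrupt or modify the allocated interventions for any participant in the trial". The sentence states a plan and not a prohibition, and its ground is that the control group receives standard care. The article supplies the full protocol as supplementary files that are not shown, and individual withdrawal wording commonly sits there.
- **That the exclusion of women with "a history of photosensitivity, or any condition affecting the lumbar region" contradicts the claim of no risk.** Excluding susceptible women is how such a risk is removed, so it is compatible with a claim about those enrolled.
- **That the consent wording in Ethical aspects admits a PBM risk.** It is generic consent language.
- **That the Blinding section repeats the error.** "Unblinding during the trial is not planned, as no adverse events are expected with PBM use" states an expectation, which is compatible with low risk.
- **That a stated share of skin reactions would be missed.** The documents give neither a reaction rate nor a capture share, so any such figure would be invented.

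**Conclusion.** The point holds as a minor correction. One of nine named effects has no evident link to either procedure, none names the skin under a contact-applied panel, and one covers it in part. The discontinuation section's claims of no risk and no adverse effects conflict directly with the low risk given in Statistical analysis.

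What is at stake is the quality of harms data on the tested intervention and the consistency of the text. The primary pain result is unaffected. Having no study-level stopping rule is reasonable for a short trial of 72 women, and none is asked for. The conclusion assumes that the form follows the lists in the article and that contact in Table 1 means contact with the skin. The size of any lost capture cannot be stated from the documents.

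**What to change.** 1. In both places in Secondary outcomes where side effects are listed, and on the form, replace the tongue item with a prompt for redness, heat, burn or other reaction at the irradiated site. Ask it in both arms, after the open question as for the other items, and report it by arm. If the tongue item has a purpose that the article does not give, state it; the skin prompt is needed either way.
2. In Study discontinuation criteria, describe the risk as low, in line with Statistical analysis, and remove the statement that PBM does not cause adverse effects or complications.

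The cost is one changed line on the form and two reworded sentences, sent to the ethics committee as an amendment in the way Ethical aspects describes. The article reports that recruitment has not begun, so every participant can be asked the same question. Sample size, visits and the primary analysis do not change.
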